### Assignment of interventions: allocation

#### Sequence generation {16a}

After baseline assessment, participants will be assigned either to the intervention or the control condition with a 1:1 allocation by means of a computerized random number generator (www.random.org) stratified by depression score (above/below HADS score of 8) [63].

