Published reports suggest that pain, functional impairment, fatigue, and comorbidities (e.g. depression and anxiety) are the major determinants of PGA [12, 13, 17], especially after remission of the inflammatory process has been achieved [12, 17]. In this sense, PGA is primarily a measure of disease impact, i.e. a mirror of current somatic symptoms and functional impairment, rather than a reliable reflexion of inflammatory activity [12, 17].

These observations support the proposal for a dual target strategy in the management of RA [16] whereby a specific target focused on the patient’s experience of the disease would be pursued in parallel with the current one, defined by disease remission, sharpened by the exclusion of PGA.

In RA, more than 70% of patients report levels of fatigue that are similar to those observed in chronic fatigue syndrome [18], and half of all patients report it as severe and of the highest priority in their list of persistent complaints [19]. These observations are similar among patients in PGA-near-remission despite being virtually devoid of joint inflammation [12]. Patients often consider that this symptom is unduly ignored by clinicians [20].

Multiple factors have been associated with fatigue observed in RA [21], reinforcing its complex and multicausal nature [22]. Depression, disability/inactivity, and sleep disturbances seem to be key drivers of fatigue [23], whereas pain and disease activity appear to play a rather minor role [22]. This complexity underlies the major challenge faced so far in the design and implementation of effective interventions.

Adjunctive non-pharmacological interventions, including exercise, counselling, occupational therapy, cognitive behavioural therapy (CBT), and other psychological interventions, have been associated with positive results [24–26]. CBT is the gold standard intervention in many mental and physical health conditions, and a valuable intervention in RA [27–29], with proven beneficial effects in chronic pain, sleep difficulties, fatigue, self-management, self-care, coping, and well-being, both in individual and group settings [30].

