#### Sample size {14}

The primary outcome of the study will be the difference in fatigue scores between the two intervention groups at week 32, controlling for baseline values. Based on the minimum clinical improvement established for RAID score and on our previous study assessing the responsiveness of RAID.7i, we expect a minimum difference in fatigue scores between the two groups of at least 3 points [54, 71, 72].

A sample size of 91 was indicated by G*Power for analysis of covariance (ANCOVA) [*α* = 0.05, 90% statistical power, effect size of 0.50]. Assuming a 30% attrition rate and rounding up for convenience, we plan to recruit a total of 120 participants (60 participants per arm).

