## Statistical methods

### Statistical methods for primary and secondary outcomes {20a}

Descriptive analysis and test differences will be used to compare the baseline demographics and participants’ characteristics as well as variables of interest, such as participant’s dropout rates, reasons for dropout, and the presence/absence and severity of negative effects.

An intention-to-treat analysis will be conducted whenever possible and complemented with per-protocol analysis if needed.

Preliminary analyses will be conducted to guarantee that the necessary assumptions for the following tests are met. Analysis of covariance (ANCOVA) will be used to assess between-group differences in fatigue scores (the primary outcome) at the 3-month follow-up after the second booster session (32nd week), controlling for baseline values. The same analytic procedure will be used to examine the between-group differences in perceived disease activity, depression, mindfulness, and self-compassion (secondary outcomes) in the 32nd week. All effect sizes will be reported.

Additionally, time × group interaction effects on fatigue levels, perceived disease activity, depression, mindfulness, and self-compassion scores across the different time points will be tested via repeated measures analysis of variance (ANOVA), within-between interaction (with Bonferroni correction).

Potential predictors of treatment response (e.g. sociodemographic factors, baseline levels of fatigue, disease impact, depression, and anxiety) will be explored through regression analyses.

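### The primary ANCOVA adjusts for baseline fatigue but omits the HADS depression stratum used in the randomisation, which gives up some precision

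*Protocol article*

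**What the plan says.** **Randomisation.** The protocol's section on sequence generation {16a} assigns participants "with a 1:1 allocation by means of a computerized random number generator" and describes the sequence as "stratified by depression score (above/below HADS score of 8". It gives no reason for choosing this factor and does not mention blocks.

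**Prognostic role.** The background section {6a} states: "Depression, disability/inactivity, and sleep disturbances seem to be key drivers of fatigue". It gives no correlation.

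**Primary model.** The sample size section {14} defines the primary outcome as the "difference in fatigue scores between the two intervention groups at week 32, controlling for baseline values". The statistical methods section {20a} names ANCOVA as the primary test and sets it "at the 3-month follow-up after the second booster session (32nd week), controlling for baseline values". The secondary outcomes at week 32 are to be analysed in the same way. The only other place where {20a} uses baseline depression as an explanatory variable is the exploratory regressions on predictors of response.

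**The concern.** A factor used to stratify the randomisation would normally also enter the primary model. Here the model is not left open. The test, the time point and the adjustment are all named, and the named adjustment is the baseline value of the outcome. An analysis that follows this text would omit the design factor.

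The effect of the omission depends on how allocation is done within strata:

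- **Balance enforced within strata.** The true variance of the treatment estimate already benefits from the balance, but a model without the stratum does not credit it. The reported standard error is then too large and the test conservative.
- **Balance not enforced.** The standard error is about right for that model, but chance differences in depression between the arms stay in the estimate and its true variance is larger than it need be.

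What is at stake is efficiency: intervals wider than they need be and a little lost power.

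The stratum itself has a small gap. A score of exactly 8 is neither above nor below 8, and that score decides which list a patient is allocated from.

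**Working it through.** **Inputs from the protocol.** 120 randomised and 30% attrition leave 120 × (1 − 0.30) = 84 completers. The section also gives "0.05, 90% statistical power, effect size of 0.50", without saying whether 0.50 is Cohen's f or d.

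**The plan's own figure.** The protocol states: "A sample size of 91 was indicated by G*Power for analysis of covariance (ANCOVA"). For two groups and one covariate, with the noncentral F distribution, the total is 45 if 0.50 is f and 171 if it is d (f = 0.25). Neither gives 91. That is a separate matter. Here it means only that power has to be shown under both readings.

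**Assumed input.** The partial correlation r between baseline depression and week-32 fatigue, given baseline fatigue, is taken as 0.1 to 0.3.

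**Step 1, variance.** Adding the covariate multiplies residual variance by (1 − r²) and the standard error by √(1 − r²).

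- r = 0.1: variance falls by 1%, SE × √0.99 = 0.995, and 84 × 0.01 = 0.84, about 1 patient.
- r = 0.3: variance falls by 9%, SE × √0.91 = 0.954, and 84 × 0.09 = 7.56, about 8 patients.

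**Step 2, power at 84 completers.** The noncentral F calculation was repeated with effect f/√(1 − R²) and one more covariate, where R² = r².

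| Partial R² | Power if d = 0.5 | Power if f = 0.5 |
|---|---|---|
| stratum omitted | 61.9% | 99.5% |
| 0 | 61.9% | 99.5% |
| 0.05 | 64.2% | 99.6% |
| 0.10 | 66.5% | 99.8% |
| 0.20 | 71.6% | 99.9% |

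The last row lies well beyond the assumed range (r = 0.3 is R² = 0.09) and is shown as an outer bound. The R² = 0 row shows the cost of the extra degree of freedom when depression adds nothing: about 0.01 percentage points of power.

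**Step 3, does the standard error match the design?** A simulation used N = 84, partial R² = 0.10, 40% of patients in the upper stratum and a correlation of 0.3 between stratum and baseline fatigue, all assumed apart from N. It ran 8,000 trials under no effect and 4,000 with d = 0.5.

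| Allocation in stratum | Stratum in model | True SD | Mean model SE | Type I error | Power |
|---|---|---|---|---|---|
| Blocks of 4 | no | 0.210 | 0.219 | 4.0% | 62.1% |
| Blocks of 4 | yes | 0.209 | 0.208 | 5.0% | 66.5% |
| No blocks | no | 0.223 | 0.220 | 5.3% | 60.8% |
| No blocks | yes | 0.213 | 0.210 | 5.5% | 64.7% |

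The simulation error of a 5% rate from 8,000 runs is √(0.05 × 0.95 / 8000) = 0.24 percentage points, so 5.3% and 5.5% are compatible with 5%.

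With blocks, the loss lies in the reported SE (0.219 against a true 0.210), while the estimator itself hardly changes. Without blocks, the reported SE is about right and the loss lies in the estimator (true SD 0.223 against 0.213).

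**The case against.** The strongest reply is that this is a small matter of efficiency in a condensed article, and that a full covariate list usually belongs in the statistical analysis plan. Neither section says its covariate list is complete. The eligibility criteria exclude severe depression and current psychological or psychiatric treatment, which narrows the HADS range and may weaken its prognostic value. If 0.50 is Cohen's f, power at 84 is already 99.5% and nothing noticeable is gained.

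Most of this stands as a limit on size. It does not remove the point, because the protocol states the adjustment twice and leaves the design factor out both times.

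A reader might infer four stronger things that the protocol does not support:

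- **That the standard error is certainly wrong for this design.** It is too large only if balance is enforced within strata, and the protocol does not say whether it is.
- **That allocation is unrestricted and the arms are likely to be unequal.** An article may leave out block details, and 60 per arm is planned. Even a 54/66 split has relative efficiency 4 × 0.45 × 0.55 = 0.99. Total arm sizes also say nothing about balance in depression, and a covariate would not change them.
- **That false positives are at risk.** They are not; any error is conservative.
- **That depression was chosen as the strongest predictor.** No reason for stratifying is given, and the background lists depression with disability/inactivity and sleep disturbances without ranking them.

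On the stratum definition, the reference to a depression score makes the subscale the natural reading. Naming it is a clarification. The score of exactly 8 is a real gap, though one of wording.

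**Conclusion.** The point holds as one of efficiency. The randomisation uses HADS depression, and the primary model as specified does not. Over an assumed partial correlation of 0.1 to 0.3, the omission is worth 1 to 9% of residual variance, or about 1 to 8 of 84 completers. If the effect size is d = 0.5, that is at most roughly 4 to 5 percentage points of power; if it is f = 0.50, almost nothing. The range rests on an assumption, since the protocol does not quantify how far depression predicts week-32 fatigue beyond baseline fatigue. If depression adds nothing, the gain is nil. The validity of the primary test is not in question. The change is still worth making, because the factor is already measured and used at randomisation and adding it costs next to nothing.

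**What to change.** In {20a}, add baseline HADS depression to the week-32 ANCOVA next to the baseline value of the outcome, for the primary and secondary outcomes, and align the wording in {14}. Either the stratum or the continuous score will do; choose one in advance. Where depression is itself the outcome, its baseline score is already the covariate.

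In {16a}, name the HADS depression subscale and assign a score of exactly 8 to one stratum, for example below 8 versus 8 or more.

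The cost is one degree of freedom and two sentences, with no new data. The trial status section reports that no patient had yet been enrolled, so on that account the stratum could be defined before the first allocation.

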#### Concealment mechanism {16b}

Allocation sequence concealment will be guaranteed by using a third party (a research member responsible only for generating the randomization schedule) and by using sealed envelopes that are opened only after patients’ enrolment.

#### Implementation {16c}

Recruiters will engage with potential participants. After the eligibility criteria have been confirmed, the allocation sequence will be generated by a computerized random number generator by the coordinator of the study (www.random.org). Another team person will assign participants to the intervention (either MITIG.RA or TAU) according to those sequences and subsequently enrol participants in the study.

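### The two sections on allocation disagree on who generates the sequence and on whether enrolment comes before or after assignment; followed literally, one of them weakens concealment

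*Protocol article*

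**What the plan says.** Three consecutive sections of the protocol article deal with allocation.

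- **Sequence generation {16a}**: "After baseline assessment, participants will be assigned either to the intervention or the control condition with a 1:1 allocation", using a web-based random number generator, stratified by whether the HADS depression score is above or below 8.
- **Concealment mechanism {16b}**: concealment rests on two things. One is "a third party (a research member responsible only for generating the randomization schedule"). The other is "sealed envelopes that are opened only after" the patient is enrolled.
- **Implementation {16c}** (the allocation section, not the one on delivering the intervention): once eligibility is confirmed, "the allocation sequence will be generated by a computerized random number generator by the coordinator of the study". A different team member then assigns participants "according to those sequences and subsequently enrol participants in the study". Envelopes are not mentioned.

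Two other sections bear on the order of steps. Who will take informed consent? {26a} requires written consent before any study procedure. Who will be blinded {17a} says that participants cannot be blinded to their arm.

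**The concern.** Concealment means that nobody who decides whether a patient enters the trial knows the next assignment until entry is final. {16b} describes a procedure that achieves this. {16c} puts assignment first and enrolment second, and gives both steps to one person.

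If the arm is known while enrolment is still open, staff or patients can withdraw, delay or decline according to the arm. Several features of this trial raise the stakes:

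- Participants know their arm, and the primary outcome is a self-rated 0–10 fatigue score. Blinding therefore gives that outcome no second line of defence.
- Eligible patients have fatigue of at least 3 and rate their symptom state below good, so a preference for the active arm is plausible. Control patients are offered the programme only afterwards (Provisions for post-trial care {30}).
- Intention-to-treat analysis is promised only where possible (Statistical methods {20a}). The article does not say whether a patient who is assigned but not yet enrolled belongs to that set.
- There is no data monitoring committee, monitoring is done by the research team, and no external audit is planned. No outside check is described that would detect arm-dependent entry.

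**Working it through.** No arithmetic applies. The point depends on no error rate, effect size or sample size, so the check is to set the sections side by side.

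| Question | Concealment mechanism {16b} | Implementation {16c} |
|---|---|---|
| Who generates the sequence? | A research member with that sole task | The study coordinator |
| Which comes first? | Enrolment, then the envelope is opened | Assignment, then enrolment |
| Who enrols? | Not stated | The team member who assigns the arm |
| Are envelopes used? | Yes | Not mentioned |
| When is the sequence generated? | Not stated | After eligibility is confirmed |

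**Generator.** {16b} limits the person to one task. A study coordinator would ordinarily have other duties. The article does not define the role: the section on the coordinating centre and steering committee {5d} mentions only leading investigators and says there is no coordinating centre. Nothing identifies the coordinator with the single-task person in {16b}.

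**Order.** {16b} makes enrolment the condition for opening the envelope. {16c} says that enrolment follows assignment. The two orders are opposite, and no other section reconciles them.

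**What is already fixed before assignment.** Consent is signed before any procedure {26a}, eligibility is confirmed {16c} and baseline assessment is complete {16a}. Under {16c}, the only step left after the arm is known is the one it calls enrolment. The opening for selective entry is therefore that last step, and not the whole screening process.

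**Consequence under each account.** If {16b} is followed, concealment is kept. If {16c} is followed literally, the arm can be known before enrolment is complete. Staff working from the document cannot do both.

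**The case against.** The strongest reply is that {16c} is loosely worded and concealment is intact. {16b} is the section on concealment, {16c} does not withdraw the envelopes, and assigning patients from a sequence is compatible with opening envelopes. With consent, eligibility and baseline already settled, enrolment in {16c} may be a mere administrative entry. {16c} also separates recruiters, generator and assigner. Because it generates the sequence after eligibility is confirmed, eligibility decisions could not be steered by an existing list.

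Much of this stands, and it rules out stronger readings that a reader might infer:

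- *Concealment is broken.* The document does not establish this. It follows only if {16c} is carried out literally, and {16b} taken alone preserves concealment.
- *The coordinator holds the list, or the assigner can read ahead.* {16c} says who generates the sequence. It does not say who keeps it, or whether the assigner sees more than the current assignment.
- *The generator in {16b} is independent of the trial.* That section calls the person a third party but also a member of the research team.
- *Patients who decline after learning their arm disappear from the analysis.* No section says that they would be excluded. Intention-to-treat analysis, though qualified, and multiple imputation are both planned.

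The reply does not remove the contradiction. That {16c} is loose wording is a guess that the text does not confirm. Nor is this detail that an article may leave to a fuller protocol, since the article addresses both points and answers each in two ways.

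**Conclusion.** The concern holds as an unresolved contradiction on a main safeguard against selection at entry. The generator and the order of enrolment and assignment are each stated in two incompatible ways. One of the two accounts, followed to the letter, weakens concealment in an open trial with a self-reported primary outcome.

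The size of any bias cannot be estimated. The document gives no figure for how many patients might be lost between assignment and enrolment, or for how they would differ from the rest, so any number would rest on invented inputs. Prior consent, eligibility and baseline assessment limit the risk but do not remove it.

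The conclusion rests on reading the stated order in {16c} as meant, and on the ordinary sense of a coordinator as someone with other trial duties. If the coordinator has no other role, the first conflict is only one of naming. The conflict over order remains in either case.

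It should be corrected before recruitment starts, because arm-dependent entry cannot be reliably undone in the analysis: patients who never enter leave no outcome data.

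**What to change.** Rewrite Implementation {16c} to agree with Concealment mechanism {16b}:

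1. The person whose only task is the schedule generates the stratified sequence. This is not the coordinator, unless the coordinator has no other role in the trial, in which case both sections should say so.
2. Consent, eligibility, baseline assessment and enrolment are recorded first, in that order.
3. Only then is the next sealed envelope in the patient's HADS stratum opened, by someone who cannot see upcoming assignments.
4. Every patient whose envelope is opened counts as randomised and is included in the intention-to-treat set.

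The cost is a change of wording and of the order of steps. {16b} already provides for the person and the envelopes, so no extra staff are needed. Trial status reports that no patient had been enrolled at that stage, so on the article's own account the correction could apply to every participant.

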### Assignment of interventions: blinding

#### Who will be blinded {17a}

Given the nature of the study, it will be impossible to blind participants regarding their allocation. However, the following types of blinding will be implemented: blind assessment (the rheumatologist performing the examinations will be blind to the patient’s allocation) and blind analysis (the researcher performing the statistical analysis will be blind to participants’ allocation).

#### Procedure for unblinding if needed {17b}

There will be no unblinding procedures due to the nature of the intervention.

### Data collection and management

#### Plans for assessment and collection of outcomes {18a}

The research team is responsible for the assessment and collection of outcomes, being the content and timing of the assessment similar to both intervention groups.

Clinical data and outcome measures will be collected online, via Reuma.pt (www.reuma.pt), the official and ethically approved national register of rheumatic patients.

Sociodemographic information will be collected from the patients’ files at baseline. Measurement of C-reactive protein levels and clinical examination and assessment of disease activity will be performed and registered at screening, baseline, and after 20 and 44 weeks by the rheumatologist. Medication monitoring and recording will be performed throughout the study, from screening to the last follow-up period.

At baseline, 8 weeks (post-intervention), 12 weeks (before the 1st booster session), and 20 weeks (before the 2nd booster session), participants will complete an online assessment battery comprising a set of validated self-report measures (see Fig. 1). This assessment will be repeated at 32 and 44 weeks to evaluate the persistence of potential therapeutic gains over time. Each patient will have private access to the questionnaires through a personal registered account. The research nurse will determine the correct completion of all measures. Those responsible for delivering the interventions will not be involved in any form of data collection and analysis over the duration of the trial.

